# Lisbon Intensive Falls Trampoline Training (LIFTT) Program for people with Parkinson’s for balance, gait, and falls: study protocol for a randomized controlled trial

**DOI:** 10.1186/s13063-023-07131-4

**Published:** 2023-02-08

**Keywords:** Falls, Trampoline training, Effectiveness, Balance, Parkinson’s disease, Randomized controlled trial

## Abstract

**Background:**

Falling and gait difficulties in people with Parkinson’s disease (PD) are associated with impaired reactive postural adjustments and impairments in attentional resources. Combined intensive balance motor and cognitive exercise can be beneficial. However, uncertainties persist regarding the true effects and safety when applying such training. Using trampoline beds may be a favorable safe environment for a highly intensive, cognitive, and balancing training approach. The primary goal of this randomized controlled trial is to assess the effects of an intensive cognitive-motor training program in a safe trampoline environment in addition to usual care on balance impairment, gait, physical capacity, fear of falling, falls frequency and severity, cognition, and clinical impairments in people with mild or moderate PD.

**Methods:**

Sixty participants diagnosed with idiopathic PD, in stage 2–4 Hoehn and Yahr, with a clinical history of gait deficits and a fall history (at least one fall in the last 6 months) will be recruited and randomly allocated to an intervention group receiving cognitive-motor trampoline training or a control group undergoing their usual care. The intervention will consist of 8-week individual training sessions (1-h training, 3 days per week) led by specialized physiotherapists that will provide progressive, challenging training, and guarantee safety. Assessment will be conducted prior to and immediately after the 8-week intervention and at 3 months follow-up after participating in the study. Primary outcome measures will be balance performance (assessed using the Mini-BEST Test and nonlinear analysis) and change in gait parameters (Motor and Cognitive Timed-Up-Go and nonlinear analysis). Secondary outcomes will be change in clinical improvement (Movement Disorder Society Unified Parkinson’s Disease Rating Scale), falls (falls weekly registry), fear of falling (assessed using the Falls Efficacy Scale), physical capacity (6-min walk test), and cognition (Montreal Cognitive Assessment).

**Discussion:**

This study will provide new evidence on the benefits of intensive cognitive-motor balance training on a trampoline for people living with PD. Better guidance on how professionals can apply safer dual-task balance and gait training in rehabilitation is needed.

**Trial registration:**

ISRCTN Registry ISRCTN13160409. Retrospectively registered on February 23, 2022

## Contributions to the literature

Frequent falls have a significant impact on the mobility and quality of life of people with Parkinson’s disease.Supervised exercise programs that challenge balance and also impose cognitive demands have been recommended to improve postural instability and fear of falling, prevent falls, and maintain mobility in people with Parkinson’s.This study represents an innovative method to manage balance and falls in Parkinson’s using trampolines to train impaired reactive postural adjustments and impairments in attentional resources in a safe environment. It represents a new guidance on how professionals can apply safer dual-task balance and gait training in rehabilitation.

## Background

Parkinson’s disease (PD) presents many challenges due to the significant functional disabilities affecting posture, gait, daily living activities, and cognition [1]. Falls have a significant impact on the mobility and quality of life of people with PD [2, 3]. They result from a complex interplay of several generic (age-related) and PD-specific fall risk factors [4]. The most frequently highlighted factors are fall history, cognitive impairment, dual tasking, disease severity, postural instability, axial rigidity, shuffling, and small-scaled gait. Frequent falling in people with PD has been highly associated with impaired reactive postural adjustments and impairments in attentional resources [5–7]. When people with PD have to divide attention between two tasks, there can be a decrease in one or both of these tasks. To ensure an appropriate performance, they typically prioritize the cognitive domain, leading to the risk of losing balance and falling due to the lack of sufficient attentional resources [5].

Supervised exercise programs that challenge balance and also impose cognitive demands have been recommended to improve postural instability and fear of falling, prevent falls, and maintain mobility in people with PD [4, 8–10].

Importantly, the combination of both cognitive and motor challenges has been shown to benefit people with PD in both physical and cognitive outcomes [11–15]. Initial research in this area concluded that 30 min once a week for 3 weeks of multiple-task gait training can be feasible in people with PD, with sustained benefits upon multiple-task walking velocity, levels of fatigue, and anxiety [11]. Later, more evidence emerged showing dual-task training can have benefits related to gait (gait speed, step length, and cadence) and balance [9, 16–18].

Even though research has shown the feasibility and safety of dual-task training [18, 19], uncertainties still exist regarding the best way to apply such motor-cognitive exercises that guarantee the highest safety of participants. In clinical practice, physiotherapists and trainers may be reluctant to add dual-task approaches because of safety issues and potential fall risks. Dual-task training was initially recommended not to be used [20] mainly because it was thought to aggravate gait disturbances and cause falls. For example, Conradsson et al. [9] reported 13 falls and an incidence rate of 0.9% during training when applying a high-intensity dual-task walking program in people with PD. Even though the authors reported that none of these events caused injury or pain that interfered with the participants’ ability to proceed with the balance training, safety continues to be a major concern when applying such programs. Given the limited evidence, such programs will thus require specific knowledge and expertise in PD to avoid placing patients at risk and/or receiving unnecessary procedures [21].

The use of trampolines could be one way to guarantee maximum safety while also intensively challenging weight shifting, dynamic changes in balance, aerobic training, strength, and dual-task interference and reduce the risk of injury if a fall should happen. Even though trampoline beds are unstable surfaces, they are expected to guarantee safety while allowing for freedom of movement and training, mimicking better real-life situations. Its use in rehabilitation has been shown to be feasible and efficient in different populations such as older adults [22], individuals with intellectual disabilities [3], and people who suffered a stroke [23]. The study by Aragão et al. [22] showed that a 14-week training on a trampoline improved the ability of older adults to recover balance during forward falls due to a higher rate of hip moment generation. A 2-week trampoline exercise program was an effective intervention to improve the motor and balance ability of school-aged children with intellectual disabilities [24]. Hahn et al. [23] also showed that both the trampoline and the control group had significant improvements in balance, gait, and falls self-efficacy compared to before the 6-week intervention (30 min sessions, 3 times a week) after stroke. In PD, we identified one study that compared the effect of an 8-week rebound therapy-based exercise program over range of motion, proprioception, and quality of life in 20 people with PD [25]. The combination of dual-task training and trampolines has not yet been reported apart from our preliminary results in a pilot study [26]. The results from our group showed that training on a trampoline bed combining balance and cognition was well received and safe for 13 people with PD [26]. Participants reported being “very satisfied” (7/13) or “satisfied” (6/13) with the program. Adverse effects were mild (“feeling tired,” excessive sweating). Participants had favorable perceived benefits (80% very useful; 20% moderately useful), and all indicated that they were willing to continue in the program and recommend it to others.

Considering the preliminary findings regarding compliance, willingness to participate, and safety, here, we aim to assess this program’s effectiveness on clinical outcomes. The primary aim of this proposed randomized controlled trial will be to assess the effects of an intensive cognitive-motor training program in a safe trampoline environment in addition to usual care on balance impairment, gait, fear of falling, falls frequency, physical capacity, cognition, and clinical impairments in people with mild or moderate PD.

## Methods

### Design

The study is a prospective, randomized controlled clinical trial, with a 3-month follow-up, with an allocation ratio of 1:1 and hypothesis type of superiority.

### Study setting

The study will be conducted in collaboration with the Portuguese Parkinson Patient Association (APDPk) and the Movement Disorders Outpatient Clinic from Hospital Garcia de Orta (MDOC-HGO) in Portugal. The program will be delivered in a community environment (trampoline fun house JumpYard) in Lisbon.

### Participants

People with PD will be recruited from the APDPk and the MDOC-HGO by the senior physiotherapist specialist (JD) and the neurologist (MG), respectively. Announcements in common social media channels (Facebook Parkinson’s groups) will also be used to recruit participants and assessed them with their respective neurologists.

Participants will be asked to sign an informed consent and understand their right to withdraw his/her consent at any time without prejudice to future medical care. Participants will be included if (a) diagnosis of idiopathic Parkinson’s disease (Movement Disorder Society Parkinson’s Disease criteria), (b) Hoehn and Yahr stages 2–4, (c) age above 18, (d) able to walk independently and currently able to tolerate a minimum 1 h of exercise, and (e) able to communicate with the investigator, to understand and comply with the study procedures.

Participants will be excluded if they have severe postural instability assessed by MDS-UDPRS Part III item 3.12 and/or severe cognitive difficulties or significant active psychiatric problems that enable the person to participate in the protocol.

### Sample size calculation

The sample size for this study was determined based on previous related interventional trials with people with PD. The sample size was determined considering a two-sided alpha level and was based on a difference between two independent group means (*T*-Student’s test). Considering a 0.7 effect size (e.g., for the FES-I outcome), for 80% power and an alpha level of 5%, a sample size of 26 subjects per group will be required. With a dropout rate set at 15%, a final sample of 60 (*n* = 30 per group) was considered optimal. So, we will include 60 people with PD living in Portugal.

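### The sample size rests on an effect of 0.7 illustrated only by a secondary outcome (FES-I), so the 80% power is not justified for any primary outcome, and 26 per group does not give 80% at 0.7 under the stated two-sided test

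*Protocol article*

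**What the plan says.** The Sample size calculation section gives a general source: "The sample size for this study was determined based on previous related interventional trials with people with PD". It says that "The sample size was determined considering a two-sided alpha level" and that the calculation "was based on a difference between two independent group means", using Student's t-test. The effect is introduced with "Considering a 0.7 effect size (e.g., for the FES-I outcome"). From this, "for 80% power and an alpha level of 5" per cent, the section concludes that "a sample size of 26 subjects per group will be required". With 15% dropout it arrives at 60 participants, 30 per group. It names no outcome other than FES-I and gives no SD or raw difference.

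The Abstract (Methods) ranks the outcomes: "Primary outcome measures will be balance performance (assessed using the Mini-BEST Test and nonlinear analysis) and change in gait parameters", the latter measured by the Motor and Cognitive Timed Up and Go (TUG) and nonlinear analysis. Among the secondary outcomes it lists "fear of falling (assessed using the Falls Efficacy Scale". The Data collection section identifies that scale as FES-I.

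**The concern.** A power statement should tell the reader what the trial can detect on the outcome that will decide it. Here the only outcome attached to the effect size is a self-reported secondary scale, in a trial where participants know whether they are training on a trampoline. Nothing in the article links 0.7 SD to the Mini-BEST Test, the TUG or the nonlinear measures. A reader who meets a null primary result beside an 80% power claim could take it as evidence against an effect, when the article has not shown which balance or gait effect the trial could detect.

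The same sentence has a second problem. The four stated inputs (effect 0.7, two-sided, 5%, 80%) fix the group size, and it is not 26. So the 80% is unsupported for the primary outcomes and is also not delivered at the effect size that was chosen.

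**Working it through.** **Inputs, all from the Sample size calculation section.** Standardised effect d = 0.7; two-sided alpha 0.05; power 0.80; two-sample t-test; 15% dropout; 30 per group. The 1:1 ratio is in the Design section.

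**Step 1: the plan's own figure.** The normal approximation is n per group = 2(z_alpha + z_power)² / d².

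- Two-sided 5%: 2(1.960 + 0.842)² / 0.49 = 32.04, so 33 per group. The exact noncentral t calculation gives 33.02, so 34 per group.
- One-sided 5%: 2(1.645 + 0.842)² / 0.49 = 25.2, so 26 per group. The exact calculation gives 25.94, so 26 per group.

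The stated 26 is therefore not reproduced under the stated two-sided test. It is reproduced exactly under a one-sided 5% test.

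**Step 2: dropout.** 26 × 1.15 = 29.9, which gives the stated 30 per group. Dividing instead, 26 / 0.85 = 30.6, gives 31. The difference is small and is not the point here. After 15% loss, 30 × 0.85 = 25.5 per group remain.

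**Step 3: power at d = 0.7, two-sided 5%.** The noncentrality parameter is d√(n/2), with 2n − 2 degrees of freedom.

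| n per group | Noncentrality | Power |
|---|---|---|
| 25.5 (30 less 15%) | 2.50 | 69% |
| 26 (stated requirement) | 2.52 | 70% |
| 30 (no loss) | 2.71 | 76% |
| 34 (exact requirement) | 2.89 | 81% |

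Even with no dropout, 80% is not reached. This gap comes from the one-sided/two-sided mismatch and not from the choice of FES-I.

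**Step 4: what the planned size can detect.** Solving the same calculation for d at 80% power and two-sided 5% gives 0.80 SD with 25.5 per group, 0.79 SD with 26 and 0.74 SD with 30.

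**Step 5: range for a primary outcome.** The article gives no effect size for any primary outcome, so the values of d below are assumptions that show only how sensitive power is to d.

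| Assumed d | Power, 26 per group | n per group for 80% |
|---|---|---|
| 0.4 | 29% | 100 |
| 0.5 | 42% | 64 |
| 0.6 | 56% | 45 |
| 0.7 | 70% | 34 |
| 0.8 | 81% | 26 |

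**The case against.** The abbreviation e.g. makes FES-I an illustration, and a t-test calculation on a standardised effect holds for any continuous outcome whose true effect is 0.7 SD. This stands. A reader might infer that the calculation cannot apply to the primary outcomes at all, and the article does not support that. What is missing is any reason to expect 0.7 SD on those outcomes.

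A reader might also infer that power for the primary outcomes is lower than for FES-I. That does not follow either: with no effect size given, the true value for balance or gait could lie on either side of 0.7. The planned analysis is a repeated measures ANOVA over three time points, whose power depends on within-person correlation, so the t-test figures are not its exact power. They do follow the method on which the article bases its sample size.

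The primary aim, in the Abstract and again at the end of the Background, includes fear of falling. It also includes falls, physical capacity and cognition, and the one explicit ranking of outcomes makes the Falls Efficacy Scale secondary. This softens the premise without removing it.

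Finally, the full protocol may hold a fuller justification. That may explain the missing detail. It would not explain why the one outcome chosen for the published calculation is secondary, or why the stated inputs do not give 26.

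Several primary measures are named, so one could go on to split the 5% between them and report lower power. The article plans no such split, and the handling of multiplicity may be left to the analysis plan, so no figure of that kind is used here.

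**Conclusion.** The concern holds in this form: the 80% power is not justified for any primary balance or gait outcome, because the only outcome offered in support of d = 0.7 is secondary. Separately, 80% is not attained at d = 0.7 under the stated test. It is about 70% with 26 per group and 69% with 25.5, and 34 per group would be required. The arithmetic uses only the article's inputs and an unadjusted two-sample t-test. How much power the trial has for Mini-BEST or TUG cannot be determined from the article.

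**What to change.** In the Sample size calculation section:

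1. Name a primary outcome, for example Mini-BEST total score at T1, and state the smallest between-group difference detectable with 80% power at two-sided 5% from 60 randomised and 15% loss. This is about 0.80 SD for an unadjusted t-test. Convert it to points with a sourced SD, which the article does not give.
2. Replace the claim that 26 per group gives 80% power with the correct figure of about 70% at d = 0.7 (two-sided 5%).
3. Keep FES-I only as an illustration for a secondary outcome, and do not call the trial 80% powered on that basis.

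The cost is rewording, one calculation and finding a source for the SD. No extra patients are needed. The stated power becomes less favourable.

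### The stated two-sided 5% t-test at effect size 0.7 has about 70% power with 26 per group, not 80%; 26 is what a one-sided test gives.

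*Protocol article*

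**What the plan says.** The Sample size calculation section of the protocol article prints every input. The size was "determined considering a two-sided alpha level and was based on a difference between two independent group means", using Student's t-test. The effect size is 0.7, with the FES-I given as an example outcome. The result is: "for 80% power and an alpha level of 5%, a sample size of 26 subjects per group will be required". The last step is the allowance for losses: "With a dropout rate set at 15%, a final sample of 60", that is, 30 per group. The Design section adds 1:1 allocation and a superiority hypothesis.

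The section mentions no one-sided test, baseline adjustment, within-person correlation or other device that would reduce the number.

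**The concern.** For a standardised difference of 0.7, 80% power and a two-sided 5% test, a quick calculation gives a little over 30 per group, so 26 looks too small. A gap of that size is not rounding or a choice between the exact and the approximate formula. It suggests that one input in the paragraph is not the one used in the calculation.

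The whole sample size rests on the 26. If it is wrong, the 80% power claimed for the trial is wrong too. Readers would then take a non-significant result as stronger evidence against a 0.7 SD effect than the design supports.

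**Working it through.** **Inputs, all from the Sample size calculation and Design sections:** two-sided test; alpha 0.05; two-sample t-test; d = 0.7 (so SD = 1); power 0.80; 1:1 allocation; dropout 15%. Stated result: 26 per group, raised to 30.

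**1. Stated inputs, normal approximation**

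n per group = 2(z₁₋α/₂ + z₁₋β)² / d² = 2(1.960 + 0.842)² / 0.49 = 32.04, rounded up to 33.

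**2. Stated inputs, exact noncentral t**

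The noncentrality is d√(n/2) on 2n − 2 degrees of freedom. Solving for 80% power gives n = 33.02, so 34 per group (33 gives 79.97%). The stated 26 is not reproduced by either method.

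**3. What does give 26**

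- One-sided 5%, d = 0.7, normal approximation: 2(1.645 + 0.842)² / 0.49 = 25.2, rounded up to 26.
- One-sided 5%, d = 0.7, noncentral t: 25.94, rounded up to 26, with power 80.1%.
- Two-sided 5%, d = 0.8, noncentral t: 25.52, also rounded up to 26.

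The first two keep the printed effect size and change the sidedness. The third keeps the sidedness and changes the effect size.

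**4. Power of the stated two-sided test at d = 0.7 (noncentral t)**

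| n per group | Situation | Power | Effect detectable with 80% power |
|---|---|---|---|
| 25 | 30 less 15%, rounded down | 67.9% | 0.81 SD |
| 25.5 | 30 × 0.85 | 68.8% | 0.80 SD |
| 26 | stated requirement | 69.7% | 0.79 SD |
| 30 | no dropout at all | 76.0% | 0.74 SD |
| 34 | needed for 80% | 81.2% | 0.69 SD |

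**5. Dropout step**

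26 / 0.85 = 30.6, so 31 per group. The 30 matches 26 × 1.15 = 29.9. The difference is one participant per group, which is minor. Starting from the correct requirement, 34 / 0.85 = 40 per group, or 80 in total against the planned 60. Starting from 33 (normal approximation), 33 / 0.85 = 38.8, so 39 per group, or 78 in total.

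**The case against.** **The cause is not proven.** The article says two-sided, and a two-sided test at d = 0.8 also rounds to 26. The slip could therefore be in the effect size rather than the sidedness. This stands as far as the cause goes: the one-sided explanation is an inference from a match. It does not touch the mismatch. With the inputs as printed, 26 is wrong on either explanation, and the same restatement corrects it.

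**The planned analysis is not a t-test.** The Data analysis section plans a two-way repeated-measures ANOVA over three time points and latent growth modelling. These use the baseline and may have more power than a single-time-point t-test. As an illustration, if the outcome were adjusted for baseline, the effective effect size would be d/√(1 − r²). With an assumed baseline-outcome correlation r = 0.5, power is 80.0% at 25 per group and 81.5% at 26; with r = 0.6 it is about 86% to 87%. So the 70% figure belongs to the t-test in the sample size paragraph and is not shown to be the power of the final analysis. But the paragraph ties its 80% to an independent-groups t-test and states no correlation, so the claim cannot rest on that gain.

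**The 0.7 is only an example, for the FES-I.** The Abstract lists the FES-I as a secondary outcome, so the calculation says little about power for the primary balance and gait measures. That is true, but it does not make the arithmetic right.

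**An article condenses the full protocol.** That excuses omissions. Here the inputs and the result are both printed, and they disagree.

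**Conclusion.** The concern holds. The stated inputs require 34 per group (33 by the normal approximation), not 26. At 26 per group the stated test has 69.7% power, about 10 percentage points below the claim. The risk of missing a true 0.7 SD effect is about 30%, half as much again as the declared 20%. Even complete retention of 60 participants leaves power at 76.0%.

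This rests on equal groups, the usual t-test assumptions, and the printed sidedness, alpha and effect size. That a one-sided setting produced the 26 is probable but not documented. The dropout rounding is incidental.

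**What to change.** Keep 60 participants and correct the Sample size calculation paragraph. It should say that, with 60 randomised and 15% dropout (about 25 to 26 evaluable per group), a two-sided 5% t-test has about 70% power for a standardised difference of 0.7 and 80% power for a difference of about 0.80. The sponsor should also say which input was misstated, the sidedness or the effect size.

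If the sponsor wants to keep 80% power at 0.7, the calculation would have to be based on a baseline-adjusted analysis, with the assumed baseline-outcome correlation stated and justified. The Data analysis section would then need to name that analysis, which it does not now do. The restatement above is sufficient without this.

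The cost is one reworded paragraph and a less favourable power figure. No participants are added. This suits a trial whose recruitment, according to the Trial status section, was due to finish in February 2023.
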